### Methods in analysis to handle protocol non-adherence and any statistical methods to handle missing data {20c}

Previous clinical trials conducted by the study team have recorded less than 10% attrition [36, 40]. In the power analysis for the present study, we have used a conservative estimate of 20% attrition. Participants who drop out, who fail to attend a study assessment, or who are lost to follow-up will not be replaced by new participants, as we have accounted for this in the sample size estimate. Missing baseline and outcome data will be summarised by study arm and reported in the CONSORT. If attrition is higher than anticipated, multiple imputation will be used to impute the AUDIT score [50], and primary and secondary analyses will be conducted with the imputed datasets.

### Plans to give access to the full protocol, participant-level data, and statistical code {31c}

The authors plan to grant full public access to trial protocols as well as statistical code and underlying participant-level data for published analyses through the Open Science Foundation (OSF) repository for the study: https://osf.io/ftqyd/.

## Oversight and monitoring

### Composition of the coordinating centre and trial steering committee {5d}

The coordinating centre is located in SolidarMed’s field office in Butha-Buthe, Lesotho. This is a secure, locked building with secure, locked rooms inside of which the study team can safely store data. The trial steering committee consists of the study PIs (a clinical psychologist and a microbiologist), the Sponsor-Investigator (a medical doctor), a psychiatrist, and two PhD candidates in clinical research. Most steering committee members meet weekly to plan and manage the trial and discuss issues that arise. They will continue to meet weekly as the study is implemented and follow-up data collected. The trial steering committee oversees data management including collection and entry of data, plans day-to-day trial implementation and supervision for interventionists, oversees participant recruitment, and reviews and addresses safety events as they occur.

### Composition of the data monitoring committee, its role, and reporting structure {21a}

A Data Safety and Monitoring Board (DSMB) has been formed, comprising of three experts in clinical trials, biostatistics, behavioural interventions, and mental health in LMIC settings who are not involved in the study and who do not have scientific, professional, or financial conflicts of interest. The DSMB meets with the study investigators at the beginning of the trial and at regular intervals thereafter to review trial progress, as well as to review non-identifying reports of adverse events and steps taken by the study team to address them. The DSMB provides guidance about any further next steps that might help protect participant safety and well-being and ensure a high level of scientific compliance. The DSMB may also be contacted outside of planned meetings if the investigators believe their input is needed. DSMB members receive an honorarium for participating in each meeting.

### Adverse event reporting and harms {22}

Study staff interacting with participants are trained to understand what constitutes an adverse event (AE). Research assistants systematically inquire about any changes in participant physical or psychological well-being at each of the study’s follow-up assessment (i.e., at 8, 20, and 32 weeks). Recording of AEs outside of these assessments (e.g., assessment reminder phone call, intervention session) occurs on an ad hoc basis. Staff members record details of the AE; study coordinators and PIs are then made aware of the event. The study PIs evaluate the severity of the AE according to the Common Terminology Criteria for Adverse Events grading system [51] and make a causality assessment of the event in relation to the study intervention according to the standards set by the International Conference on Harmonisation, topic E2A [52]. Relatedness options of the study intervention to the AE are definitely unrelated, unlikely, possibly, probably, or definitely related.

In the event of a serious adverse event (SAE) that is “possibly,” “probably,” or “definitely” related to the study intervention, the event is reported to the ethics committee in Lesotho within 15 days of the study team learning of the event [53]. All other SAEs and AEs are reported to the ethics committee annually. Participants who terminate the study with reported ongoing SAEs that are “possibly,” “probably,” or “definitely” related to the study intervention are followed up until resolution or stabilisation of the SAE, for up to 6 months after study termination. If immediate safety and protective measures must be taken during the conduct of the study, the study PIs notify the ethics committee of these measures, and of the circumstances necessitating them, within 7 days. In the primary publication describing the trial results, a summary of all AEs will be provided according to severity and relatedness to the study intervention.

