### Intervention description {11a}

#### mhGAP-Standard

mhGAP-Standard refers to a standardised intervention consisting of 4 in-person sessions based on the psychosocial interventions described in the WHO’s mhGAP module for substance use [15]. mhGAP is a flexible intervention guide designed to equip non-specialist providers in LMIC settings with the skills to deliver treatment for mental health and neurological conditions [14]. The intervention components are primarily focused on brief motivational interviewing, identifying triggers for use and high-risk situations, and problem-solving strategies to reduce or stop alcohol use. Participants are asked to practice skills learned in between sessions. The intervention uses a harm reduction approach, meaning that participants do not need to stop using alcohol altogether. Sessions last approximately 45–60 min each and are designed to be delivered approximately weekly, although in practice this is challenging due to scheduling difficulties and distance to the clinic. Interventionists have the option to deliver up to two additional “booster sessions” to participants who may benefit. Supplementary Table 1 provides an overview of the content covered in each session.

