#### mhGAP-Remote

Participants in mhGAP-Remote receive 1 in-person session covering the core skills of mhGAP used in the mhGAP-Standard arm, followed by standardised SMSs for a period of 8 weeks that reinforce the intervention content learned. An example SMS is, “Identify your triggers. Name a person, place, or thing that makes you want to drink alcohol. Choose one and make a plan not to interact with it this week.” SMSs are sent to participants on average twice per week at standardised days and times set by the study team. A test SMS is sent to the participant’s phone prior to them leaving the first session to ensure the phone can adequately receive SMSs and that the participant understands the delivery format. Interventionists schedule a brief check-in call with participants 2 weeks after the in-person session to ensure participants are receiving the study-related SMSs and to troubleshoot any barriers to implementing skills learned. Participants are also able to request brief telephonic support from the interventionist if they struggle to implement the skills learned by reaching out to their interventionist via SMS or phone call to request this support.

To derive the standardised SMSs used in mhGAP-Remote, formative qualitative work was conducted by the study team to gather community feedback on the content of the SMSs. SMSs were drafted based on material covered in the mhGAP psychosocial interventions for substance use. A trained member of the study team conducted in-depth interviews with 28 community members, in which they gave input on the clarity, content, and utility of each SMS. Based on this feedback, the study team (comprised of Sesotho and English speakers) adapted the content of the SMSs to improve clarity as well as to fit within the 150-character limit used by the programme sending SMSs. Additional SMSs were added after the mhGAP-Remote intervention manual was finalised, as we wanted to ensure that all important content from the in-person session was reinforced via the SMSs. These additional SMSs were reviewed as a team and changes made to ensure clarity. All SMSs underwent a forward- and backward-translation process between English and Sesotho. The final list of standardised SMSs consists of 18 SMSs. See Supplementary Table 2 for a list of the intervention SMSs and timing of delivery.

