#### Interventionist training and supervision

Of the two study interventionists, one has a bachelor’s degree in social work and the other in pastoral counselling. Both followed a systematic training process to learn the study interventions. First, they received a general training using the WHO’s provided mhGAP training for healthcare providers, which took place over 3 days and covered the following topics: introduction to mhGAP, essential care and psychotherapy practice, substance use, depression, and self-harm/suicide. This general training was also provided to other healthcare providers in the area as part of local capacity building. 

This general training was then followed by specific training in the intervention manuals developed for each treatment arm; this training was only provided to study interventionists. Study specific training included discussions on cultural and language appropriateness to increase cultural relevance of the material, motivational interviewing theory, following a session agenda and structure while adapting content to participant needs, and research protocol revision for special cases (e.g. participants with other mental health or chronic condition comorbidities). The training ended with two role-play practices for each treatment arm manual, which were audio-recorded. There was a total of 14 h of role-play practice for each interventionist. The first role-play practices were conducted in English to facilitate training evaluation by the main trainers. The remainder of role-play practices were conducted in Sesotho and evaluated by a Sesotho-speaking research team member who was trained on using a fidelity monitoring form to evaluate the core content of the intervention sessions as well as intervention process. Once fidelity was above 75%, interventionists were considered trained and ready to each start with pilot cases (up to 5 each) and subsequently with trial participants. Ongoing training continues with weekly group supervision sessions throughout the trial. Oversight of the training and supervision were provided by a clinical psychologist ([name]) and a psychiatrist ([name]), both with prior experience in training and supervising lay providers [30, 31].

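### Ad hoc AE recording between the blinded assessments has more scheduled openings in mhGAP-Standard than in mhGAP-Remote, so a pooled AE summary could show modestly fewer events in Remote through contact alone

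*Protocol article*

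**What the plan says.** Section {22}, Adverse event reporting and harms, sets up two routes. At the 8-, 20- and 32-week assessments, "Research assistants systematically inquire about any changes in participant physical or psychological well-being". Elsewhere the rule is: "Recording of AEs outside of these assessments (e.g., assessment reminder phone call, intervention session) occurs on an ad hoc basis". For the main publication, "a summary of all AEs will be provided according to severity and relatedness to the study intervention". No separation of the two routes is stated.

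The arms differ in how often an interventionist is scheduled to see or call a participant. Section {11a} gives mhGAP-Standard four in-person sessions, and "Interventionists have the option to deliver up to two additional" booster sessions. mhGAP-Remote has one in-person session, after which "Interventionists schedule a brief check-in call with participants 2 weeks after the in-person session". The stated aims of that call are to confirm that the SMSs arrive and to deal with barriers to using the skills. Beyond it, "Participants are also able to request brief telephonic support from the interventionist if they struggle to implement the skills learned".

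Section {17a} blinds the assessors but not the intervention providers. Withdrawal is foreseen in three places: the exclusion criteria, the referral provision in section {11b}, and a symptom list that participants keep (section {30}).

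**The concern.** Ad hoc recording needs an occasion, and the design schedules more occasions in one arm than in the other. If the same event happens equally often in both arms, Standard offers more chances for someone to note it. The notes are made by staff who know the allocation. Once these records are merged with those from the blinded enquiry, a reader who compares arms cannot tell a difference in harm from a difference in contact. Any distortion would tend towards fewer recorded events in Remote, the arm hypothesised to be superior.

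There is a smaller, practical side. The referral route in section {11b} works only when the team learns of symptoms. Between the first session and the first systematic enquiry, Remote has one scheduled conversation, and safety is not among its stated purposes.

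**Working it through.** The plan gives no figure for AE capture, so there is none to reproduce, and the sample size is not affected. The check is a contact count followed by an illustration.

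**Scheduled interventionist contacts after session 1** (section {11a})

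- Standard: 4 − 1 = 3; with both boosters, 6 − 1 = 5.
- Remote: 0 sessions + 1 call = 1; more only if the participant asks.

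**Timing.** Assume session 1 falls in week 1 after randomisation. The Remote call is then in week 1 + 2 = 3. An on-time first enquiry comes 8 − 1 = 7 weeks after the session. The visit window in section {13} is 6 to 16 weeks, so the gap could reach 16 − 1 = 15 weeks.

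**Illustration.** Let p be the chance that one contact leads to a record of an event that has occurred, q the chance that the blinded assessments capture it, and k the number of contacts. The documents give neither p nor q; both are assumptions. With independent contacts, all attended and all after the event,

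capture = 1 − (1 − q)(1 − p)^k.

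With p = 0.2:

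| q | Standard, k = 3 | Remote, k = 1 | Ratio |
|---|---|---|---|
| 0 | 1 − 0.512 = 0.488 | 1 − 0.8 = 0.200 | 2.44 |
| 0.5 | 1 − 0.5 × 0.512 = 0.744 | 1 − 0.5 × 0.8 = 0.600 | 1.24 |
| 0.8 | 1 − 0.2 × 0.512 = 0.898 | 1 − 0.2 × 0.8 = 0.840 | 1.07 |

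Over p = 0.1 to 0.5 the ratio runs from 1.75 to 2.71 at q = 0, from 1.16 to 1.28 at q = 0.5, and from 1.04 to 1.09 at q = 0.8. The q = 0 row describes the ad hoc route alone, not the total.

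**Sensitivity to the contact count**, at p = 0.2 and q = 0.5:

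- Both boosters given (k = 5 against 1): 1 − 0.5 × 0.328 = 0.836; 0.836 / 0.600 = 1.39.
- One on-request Remote contact (3 against 2): 1 − 0.5 × 0.64 = 0.680; 0.744 / 0.680 = 1.09.
- One assessment reminder call in each arm (4 against 2; the number of calls is an assumption): 1 − 0.5 × 0.4096 = 0.795; 0.795 / 0.680 = 1.17.
- Three such calls in each arm (6 against 4): 1 − 0.5 × 0.262 = 0.869; 0.869 / 0.795 = 1.09.
- Event after Standard session 3 and after the Remote call (1 against 0): 0.600 / 0.500 = 1.20.

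The direction is the same in every case, and the size depends mainly on q.

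**The case against.** The strongest reply is that the plan contains no error here. The systematic enquiry is the same in both arms, is made three times and is done by blinded assessors. Ad hoc notes come on top of it, and "Study staff interacting with participants are trained to understand what constitutes an adverse event". Withdrawal that needs medical care is a salient event, so q may well be high, and at q = 0.8 the ratio is at most 1.09 with three contacts against one. The simple count also leaves out the reminder calls, which the protocol names as an ad hoc source and which serve assessments that both arms have. It assumes that every Standard session takes place, although section {11a} admits that weekly delivery is difficult. No between-arm test of AEs is stated. All of this stands and limits the size of the point. It does not make the ad hoc opportunities equal.

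A reader might go further and infer that interventionists do not ask about withdrawal, or that Remote participants are left unprotected. The documents do not support that. Section {22} governs recording, not what is asked. The manuals contain scripts that are not shown and may include such a question. Higher-risk drinkers and people with specified risk conditions are excluded, a referral route exists, and participants hold a symptom list. On supervision, "Ongoing training continues with weekly group supervision sessions throughout the trial". The steering committee handles safety events as they occur, and a data safety and monitoring board reviews AE reports.

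**Conclusion.** The point holds in a limited form. The ad hoc rule is stated, the scheduled interventionist contacts after session 1 are 3 to 5 against 1 plus requests, and the staff at those contacts are unblinded. A pooled summary of all AEs could therefore show modestly fewer events in Remote for reasons of contact alone. The size is unknown. With three contacts against one and p between 0.1 and 0.5, the assumed model gives a Standard-to-Remote capture ratio of 1.16 to 1.28 if the blinded enquiry finds half of the events, and 1.04 to 1.09 if it finds 80%. Reminder calls and on-request support pull the ratio down; boosters push it up. The rate of withdrawal after the exclusions is not given, so no number of missed events can be stated.

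It would be wrong to read this as a demonstrated bias in the safety results or as a threat to the superiority claim, which concerns AUDIT change. The change is worth making because it is cheap; the trial's main conclusion does not depend on it.

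**What to change.** **Reporting.** In section {22}, state that AEs will be reported by arm. Make events elicited at the blinded 8-, 20- and 32-week assessments the main between-arm summary, and list ad hoc AEs separately by arm and source (session, check-in call, on-request contact, reminder call). An event already noted ad hoc should still count in the main summary when it is reported again at an assessment; otherwise that summary would lose events mainly in Standard. This costs one table split and needs the source of each AE to be on record. It can be done even if nothing else changes.

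**Collection.** In addition to ad hoc recording, so that spontaneous reports are kept, and unless the manuals already include it, add one yes/no withdrawal item. Base it on the existing symptom list and let it cover the time since session 1. Ask it in identical words at the 2-week Remote call and at the Standard session nearest two weeks after session 1. A yes goes to the section {11b} referral route and to the AE record.

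The item lengthens contacts slightly and needs one REDCap field and an ethics amendment. It helps only contacts still to come, which may be few because recruitment was expected to end in April 2024, and it makes capture differ before and after the change. It is asked by unblinded staff, so its results belong outside the main summary. The Standard session may be late or missed. The documents do not show that withdrawal occurs around two weeks, so the item may mainly record past events.

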### Frequency and plans for auditing trial conduct {23}

We do not have plans for external trial auditing. Trial conduct and data are monitored via the trial steering committee and the DSMB, as described above. Yearly reports on study progress and trial conduct are sent to the ethics committee. If concerns arise regarding trial conduct, the study team may appoint an independent auditor to identify and resolve these concerns.

### Plans for communicating important protocol amendments to relevant parties {25}

Protocol amendments are decided on jointly by the study PIs and Sponsor-Investigator. Input from other study investigators and team members is sought to inform the decision for protocol amendments. Any protocol amendments must first be approved by the locally responsible ethics committee. Once approved, protocol amendments are communicated to the study team through email or routine meetings. As appropriate, changes are made to the study’s trial registration page at clinicaltrials.gov. Protocol changes that directly influence participants’ experience in the trial and which would also require a new consent form, are communicated to trial participants at their subsequent study visit, where the updated consent form would be signed.

### Dissemination plans {31a}

Findings of this study will be disseminated through peer-reviewed journal articles, conference presentations, and sharing of code, protocols, and manuscripts on open-access platforms such as OSF. The results of this trial will also be shared at relevant stakeholder meetings in Lesotho, such as via the Ministry of Health and community outreach, as well as internationally. Publication preference will be given to journals with an open access publication model. Study investigators will have the opportunity to contribute to the publication of results. To facilitate capacity building and foster academic careers in Lesotho, the study team encourages Basotho collaborators to contribute to publications resulting from this study.

## Discussion

The goal of this open-label randomised trial is to test the relative effectiveness of mhGAP-Remote versus mhGAP-Standard on alcohol use. The study uses a mix of self-report (primary) and biological (secondary) assessments to measure alcohol use, as well as exploratory assessments of the intervention’s effect on liver enzymes and HIV viral load (for subsample with HIV). The exploratory data on liver enzyme tests will provide biologically supportive evidence of the effect of alcohol consumption reduction on liver function. Data on HIV viral load will add to the limited data about whether behavioural interventions for alcohol use or other mental health problems translate into changes in HIV viral load [54–56]. Overall, information from this trial will provide data on the extent to which a primarily SMS-delivered intervention can effectively reduce alcohol use in a mainly rural LMIC setting, where very few human resources dedicated to mental health exist [57–59].

Although mhGAP-Remote is a novel intervention specifically developed for the current study, prior research has used SMSs to improve alcohol treatment effectiveness. One study in Uganda for people with HIV compared the effectiveness of booster sessions using either technology (SMSs or interactive voice recordings) to provider-delivered phone calls [19]. The study found that these interventions were more effective than standard of care (providing brief advice) on self-reported alcohol use, but not in the assessment using PEth. Several other studies have examined delivery of a primarily or completely SMS-based intervention after post-injury discharge from the hospital [22, 23] or after inpatient detoxification [21]. However, none of these studies tested the premise of using SMSs as an alternate to in-person provider-delivered care for alcohol use, which is the standard approach to delivering treatment. Nevertheless, these SMS-based interventions for alcohol use appear to be feasible and acceptable in sub-Saharan Africa, including in Uganda, Tanzania, South Africa, and Nigeria [19, 23, 24, 60]. These interventions also require fewer resources to deliver than standard interventions requiring in-person delivery, making them especially appropriate for delivery in LMIC settings [60]. The results of this study will therefore add to this fast-developing literature and inform future efforts to disseminate and scale-up effective interventions for alcohol use in low-resource settings.

This trial has strengths and limitations. With regard to strengths, the study uses a randomised design to assess an innovative intervention with high potential for scale-up and evaluates the outcomes using blinded assessors. Study limitations include limited external validity based on study selection criteria, which includes individuals who have regular access to a mobile phone. Moreover, the effectiveness of mhGAP-Remote depends on successful delivery of SMSs and active engagement by participants with the messages. Prior research with an SMS-derived intervention for alcohol use reports challenges with SMS delivery [23]. The system used to deliver the SMSs in the current study can register whether the message was sent correctly, but not whether the SMS was read. As a result, measuring objective adherence to the mhGAP-Remote intervention will be limited to participant self-report.

Overall, this study will inform the effectiveness of a brief, scalable, low-resource intervention to reduce unhealthy alcohol use. This study has the potential to inform practice and policy in Lesotho and other remote, resource-constrained environments by testing a combined in-person plus SMS-based intervention that can likely reach a greater number of people with fewer human resources.

